### Decision aid

The DA was developed and piloted as part of this study. The DA and questionnaires for evaluation were programmed in Unipark, an online survey tool (QuestBack GmbH, Cologne, Germany). The structure of the DA was based on that of Mathieu et al. [19]. The DA was conceptualized as an interactive online tool consisting of a static information part and an interactive part.

We conducted a pilot study in March 2014, which showed that our study methods were feasible and acceptable to women aged 50. This quantitative pilot, to which 300 women were invited of which 53 participated, also showed that women accessed the DA and worked through it and that the questionnaires were accessed and answered. The pilot indicated that about a third of women dropped-out of the study prematurely. In a preceding qualitative pre-test both DA and questionnaires were evaluated with women of the target group through think-aloud protocols. The DA was additionally qualitatively piloted with experts from the National Network Women and Health.

In line with IPDAS criteria [25], the DA presents the options of choice (participation or non-participation in the MSP) in a decision-relevant context. The advantages and disadvantages of the MSP and their probabilities are described. These include the probabilities of a positive and negative screening result in absolute numbers supported by graphic presentations to allow women to form a realistic expectation regarding the initial outcome of the screening. We explain overdiagnosis, overtreatment, and the procedure following a positive result. Positive and negative information are presented in a balanced way according to current evidence. Step-by-step navigation through the websites of the interactive online DA facilitates a structured progress. Participants receive tailored feedback based on previous entries directly before making the decision. The studies from which the data for the DA originate are cited and provide the participants with easy access to the original sources via links.

A structured decision-making process in several steps is at the core of the DA. Participants have the opportunity to express personal values that are relevant for the decision and to clarify these for themselves. Participants have the option of printing their personal results and the static information section at the end [see Additional file 1] and to discuss matters with others. There is also an input window for remaining questions at the end of the DA.

#### Information part

The information part of the DA contains the standard information that women receive together with the invitation to the MSP [22]. The DA specifies all event probabilities based on the same population of 200 women over 20 years. In the presentation of outcome probabilities, the information part goes beyond the standard information. All probabilities are additionally represented as crowd-figure pictograms [see Additional file 1], thereby simultaneously indicating the positive and negative frames of outcomes. This type of pictorial information is beneficial [26]. Additionally, the probability of dying from breast cancer is presented in relation to the likelihood of all-cause mortality. Uncertainty in the evidence is described.

#### Interactive part

The interactive part consists of three steps. In the first step, the women assign the information items to the following categories: (1) in favour of mammography screening; (2) neither for nor against such screening; and (3) against the screening. In the second step, the women rate each point according to its importance in the decision. In the third step, the women make a decision. Through this approach, the importance of a personal value-based assessment of information is highlighted. An additional PDF file shows this in greater detail [see Additional file 1].

### Consent and data collection

The letter of invitation to the study, detailed study information, a consent form, and a return envelope will be sent by post 3 weeks in advance of the estimated date of receipt of the invitation to the MSP. The consent form will also provide for the possibility of specifying that the recipient does not have access to an email address. To increase the response rate, 1 week after the written invitation to participate in the study, a reminder and thank-you postcard will be mailed out.

Three weeks after the invitation is sent out, all women who gave informed consent and provided us with an email address will be emailed the link to the baseline questionnaire (T1). Women whose consent form is received 3-5 weeks after the invitation will receive the link at 5 weeks after the invitation. Women whose consent form is received later than 5 weeks after the invitation will receive the link at 7 weeks.

The link to the second assessment (T2) will be sent to participants 2 weeks after the first email. Women will be randomly assigned to the intervention or control group, and accordingly, receive a link either to the DA and second assessment or only to the second assessment. The link to the third assessment (T3) will be sent to the women 3 months after T2 when the screening appointment is assumed to have passed. A reminder and thank you will be emailed to all women who initially agreed to participate 10 days after sending the survey link at T1, T2, and T3.

### Primary outcome measure

The questionnaire was developed as part of another project (InEMa) and adapted for online use as well as for the evaluation of an intervention. For an overview of study outcome measures, see Table 1.

**Table 1 Tab1:** Outcome measures

Measures	T1	T2	T3
Intention to participate in the MSP	X	X	
Uptake of the MSP			X
Attitude	X	X	X
Knowledge	X	X	X
Perceived behavioural control	X	X	
Subjective norms	X	X	
Decisional conflict	X	X	X
Decision regret			X
Result of the MSP			X
Result and acceptability of the DA		X	
Invitation status		X	
Decision stage	X		
Use of/experience with other screenings	X		
eHealth literacy	X		
Internet use	X		
Demographics	X		

*Informed choice* will be measured according to the three-dimensional classification framework of Marteau et al. [11], which covers knowledge, attitude, and implementation. The individual dimensions function additionally as secondary outcomes and are described below.

### Secondary outcome measures

*Intention to participate in the MSP* will be measured using one item regarding intention to participate in the next 3 months (yes/no/undecided).

*Uptake of the MSP* will be measured using one item regarding participation in the last 3 months (MSP/opportunistic screening/none).

*Attitude* will be measured using four items adapted from Marteau et al. [11] and according to the reasoned action approach of Fishbein and Ajzen [27]. Three semantic differentials (important/unimportant; a good thing/a bad thing; beneficial/harmful) will assess instrumental attitude. One semantic differential will assesses experiential attitude (pleasant/unpleasant). Items will be rated on a five-point scale.

*Knowledge* will be measured using seven multiple choice items, with two to four answer options. The questions will cover the following: (1) screening for people without symptoms; (2) frequency of positive screening results; (3) meaning of a positive result; (4) potential to detect every cancer; (5) more diagnoses with the MSP; (6) more breast cancer deaths without the MSP; and (7) overdiagnosis and overtreatment. For each item, “do not know” will be offered as an option. Most questions will ask for nun-numeric information. Only Question 2 will ask for numeric information through four ranges of values covering the base population used in the question. This information is considered to be important as all women participating in the MSP will receive a result and a realistic expectation on the probability of both positive and negative results is important.

*Perceived behavioural control* will be measured using two items developed following the reasoned action approach of Fishbein and Ajzen [27] and rated on a five-point scale (“Whether I participate in the MSP is up to me”; “If I wanted to, I could participate in the MSP”). Additionally, 15 items (four items at T2 and T3) measuring control beliefs will be rated on a five-point scale with the anchors of “agree” and “disagree”. The items will assess logistic barriers (e.g. not having time for the appointment), trust in the MSP, and fear of pain.

*Subjective norms* will be measured using two items developed according to the reasoned action approach of Fishbein and Ajzen [27] and rated on a five-point scale (“Most people who are important to me think that I should/should not participate in the MSP”; “Most people like me would/would not participate in the MSP”). Additionally, five items will measure normative beliefs rated on a five-point scale, ranging from “advise” to “disadvise” with the additional option of “no advice”. These items will assess the direction of advice of doctors, family, and friends.

*Decisional conflict* will be measured using the SURE (Sure of myself; Understand information; Risk-benefit ratio; Encouragement) test [28]. This four-item test with the answer options yes and no will assesses knowledge of options, clarity of importance of advantages and disadvantages, sufficient level of support, and being sure about the best choice. Since no German translation of this scale is available, the scale was translated as part of this study, and indices of reliability and validity will be published.

*Decision regret* will be measured using the Decision Regret Scale [29]. The five items will be rated on a five-point scale (“strongly agree” to “strongly disagree”). Since no German translation of this scale is available, the scale was translated as part of this study, and indices of reliability and validity will be published.

*Result of the MSP* will be assessed using two items regarding the result of the MSP and the result of further diagnostics. The answers will allow grouping into four categories: (1) negative result; (2) false-positive result; (3) true-positive result, and (4) positive result with further diagnostics pending.

*Result and acceptability of the DA* will be measured using one item assessing whether the tailored graphic in the DA was balanced, and four items will assess acceptability of the DA regarding length, amount of information (too much/too little/just right), one-sidedness (pro/balanced/against), and helpfulness in decision making (yes/neither/no).

*Invitation status* will be measured using two items assessing whether an invitation was received and whether the appointment specified in the invitation had already passed.

*Decision stage* will be measured using one item following IPDAS criteria with the answer options being “not thought about it”, “contemplating it”, “close to deciding”, and “choice already made”.

*Use of/experience with other screenings* will be measured using items on (1) the use of other screenings and (2) ever having received a false-positive screening result (including false-positive mammogram).

*eHealth literacy* will be measured using the eHealth Literacy Scale [30]. Its German translation has recently been validated [31].

*Internet use* will be measured using two items regarding time spent seeking information online and importance of the Internet for health information.

*Demographics* will be measured using items assessing education level, main language, health insurance, participation in a health insurance bonus programme, and breast cancer in a first-degree female relative.

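### The T3 uptake item looks back 3 months from a questionnaire sent 3 months after T2, so screenings between the MSP invitation and T2 can be missed and informed choice misclassified

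*Protocol article*

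**What the plan says.** All references are to the protocol article.

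**Schedule** (Consent and data collection). The study letter "will be sent by post 3 weeks in advance of the estimated date of receipt of the invitation to the MSP". The T1 link then goes out in three waves, counted from the study letter:
- "Three weeks after the invitation is sent out, all women who gave informed consent and provided us with an email address" are emailed the link.
- "Women whose consent form is received 3-5 weeks after the invitation will receive the link at 5 weeks after the invitation".
- Anyone whose form comes back later still gets it at week 7.

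T2 follows 2 weeks after the T1 email, and in the intervention arm it carries the decision aid (DA). The T3 link "will be sent to the women 3 months after T2 when the screening appointment is assumed to have passed". Each link is followed by a reminder after 10 days.

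**Uptake** (Secondary outcome measures). It "will be measured using one item regarding participation in the last 3 months", with the answers MSP, opportunistic screening or none. Table 1 lists it at T3 only.

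**Related items.** Invitation status, listed at T2 only, asks whether an invitation has arrived and "whether the appointment specified in the invitation had already passed". Two T3 items ask about the screening result and any further diagnostics; no look-back is stated for them.

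**Primary outcome** (Primary outcome measure; Background). Informed choice combines knowledge, attitude and implementation. The Background section adds that the MSP invitation names an appointment, but not how far ahead it lies.

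**The concern.** The recall window and the interval from T2 to T3 have the same length, so the window opens at T2 and not at the MSP invitation. The invitation is expected before T2 in every wave. A woman whose appointment fell between the two has attended, yet the only uptake item does not ask about that period.

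Uptake feeds the implementation part of the primary outcome. A wrong entry can change a woman's classification as informed or not. That would affect both the comparison between arms and the level of informed choice under usual care, which the Discussion names as a result of interest. A recall window that is too short cannot be repaired in the analysis unless another item happens to hold the information.

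**Working it through.** **1. Timeline.** Inputs: T1 at week 3, 5 or 7 after the study letter; study letter 3 weeks before the estimated MSP invitation; T2 = T1 + 2 weeks; T3 link = T2 + 3 months (taken as 13 weeks from the T2 link); reminder 10 days later (10/7 = 1.4 weeks). In weeks from the estimated MSP invitation:

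| Wave | T1 | T2 | T3 link | Look-back opens, T3 answered on day of link | Look-back opens, T3 answered at reminder |
|---|---|---|---|---|---|
| first | 3 − 3 = 0 | 2 | 15 | 15 − 13 = 2 | 3.4 |
| second | 5 − 3 = 2 | 4 | 17 | 17 − 13 = 4 | 5.4 |
| third | 7 − 3 = 4 | 6 | 19 | 19 − 13 = 6 | 7.4 |

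The uncovered stretch after the MSP invitation is 2 to 6 weeks, or about 3.4 to 7.4 weeks for those who answer at the reminder. No earlier uptake item covers it.

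**2. Effect on classification.** Take a woman with good knowledge who was screened in the uncovered stretch and answers literally (*none*):

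| Attitude | True status | Recorded status |
|---|---|---|
| favourable | attended, congruent: informed | not attended, incongruent: not informed |
| unfavourable | attended, incongruent: not informed | not attended, congruent: informed |

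The error runs both ways. A woman with poor knowledge is not informed in either case.

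**3. The plan's sample size.** The number invited reproduces: 740 / (0.15 × 2/3) = 7400. The article states no control rate for the 370 per arm. With the one-sided formula n = [z₀.₉₅√(2p̄q̄) + z₀.₈₀√(p₁q₁ + p₂q₂)]² / δ² and δ = 0.07, 370 results at a control rate of about 14.4% or 78.6%. These rates are back-solved and are not in the article. At 48%, one of the rates quoted in the Background section, the formula gives 630 per arm.

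**4. Illustration of size.** Suppose a share s of truly informed choices is lost equally in both arms. The observed difference is 7 × (1 − s) points. Power at 370 per arm, one-sided 5%, is Φ{[√n·δ − z₀.₉₅√(2p̄q̄)] / √(p₁q₁ + p₂q₂)} at the reduced rates:

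| s (assumed) | Difference (points) | Power, control 14.4% | Power, control 78.6% |
|---|---|---|---|
| 0 | 7.00 | 80.0% | 80.0% |
| 5% | 6.65 | 77.8% | 70.5% |
| 10% | 6.30 | 75.4% | 62.1% |
| 20% | 5.60 | 70.2% | 48.4% |

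The documents give neither s nor the control rate. The table also leaves out the opposite error (second row of step 2), so it shows sensitivity and is not an estimate.

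**The case against.** **The wording is paraphrased.** The questionnaire is not shown, and a journal article condenses. Some women may also report a slightly older screening. This stands as a reason to say *can be recorded*. It does not remove the point, because window and schedule are both stated and do not fit together.

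**Other items may recover these women.** A woman who reports a screening result at T3 has attended, and the T2 item flags appointments that have passed. This stands in part. The article does not say that the result items are used to establish uptake, or whether they are shown to women who answered *none*. The T2 item records that a date has passed, not that she attended.

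**The T2 item does not show that early appointments are expected.** It belongs to a status check that also finds women not yet invited. Moreover, the MSP invitation date is only estimated, and a later invitation shrinks the gap. This is fair: the item shows that early appointments are possible, not that they are common.

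**The window starts when the DA is sent.** Attendance before T2 cannot be an effect of the DA, so counting only later uptake might be deliberate. The premise is right and justifies a sensitivity analysis. It does not justify recording an actual attender as a non-attender, since her attitude is then compared with behaviour that did not occur.

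**T3 uptake may not be the implementation component.** The Abstract writes of decision/implementation, and no time point is fixed for the primary outcome. If T2 intention were used instead, its question about the next 3 months fits a woman already screened no better.

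**Conclusion.** The mismatch holds. Read literally, the uptake item misses screenings in the 2 to 6 weeks between the estimated MSP invitation and T2, and in about the first 10 days after T2 for women who answer at the T3 reminder. Implementation can therefore be misclassified in either direction. This rests on a literal answer, on T3 uptake serving as the implementation component, and on invitations arriving near the estimated date.

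A reader might infer more: that all women screened before T2 will be recorded as non-attenders and that the trial loses much of its power. For example, assuming that 80% of informed choosers attend and that 10% to 40% of attenders fall outside the window gives differences of 6.4 to 4.8 points, and power as low as 37% at a control rate of 78.5%. The documents do not support that reading. They give no interval from invitation to appointment, no share screened early and no control rate, and the calculation ignores the error in the other direction. A small affected share, with little loss, is equally compatible with them.

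Severity: should-fix. The fault lies in a component of the primary outcome and is cheap to remove, but its size is unknown.

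**What to change.** 1. Extend the T3 uptake look-back to the whole period from the MSP invitation, for example since the MSP invitation or the start of the study. Add a fixed calendar anchor, so that the item also works for women not invited or screened opportunistically.
2. Ask for the month of attendance.
3. Add an already-attended answer at T2, worded so that it refers to the time before the T2 email.
4. State one derivation rule for uptake that uses T2 and T3 together and cross-checks against the T3 result items.
5. Keep all randomised women in the primary analysis with their true attendance status. Add a sensitivity analysis excluding women screened before the T2 link, whose attendance the DA could not have influenced.

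The cost is a change of wording in a few online items, one derivation rule and one extra analysis. The downside is a slightly longer recall period.

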### Sample size

Sample size was calculated using G* Power for the primary outcome (informed choice). Based on the study of Mathieu et al. [19], we determined a difference in the proportion of informed choices of 7 percentage points as the minimum clinically important difference for the power calculation. A sample size of 740 women (370 per arm based on a 1:1 allocation ratio) will enable the detection of a between-group difference of 7 percentage points given 80 % power and a 5 % (one-tailed) significance level. Allowing for an estimated response rate of 15 % and early drop-out of one-third of initial participants, we aim to invite 7400 women to take part in the study.

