The present study aims to assess the effect of an interactive online DA on informed choice in a randomized controlled trial using a representative sample. The primary objective is to evaluate whether the DA results in more women making an informed choice. The secondary objectives are to evaluate whether the DA (1) improves knowledge of the MSP, (2) clarifies attitudes on the MSP, (3) changes intentions to participate in the MSP, (4) is affected by background factors (e.g. education level) in its influence on the primary and secondary outcomes, (5) lowers decisional conflicts, and (6) differs in its long-term effects depending on the outcome group of the screening (true positive, false positive, negative).

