### Data analysis

The data will be exported from Unipark and analysed with SPSS version 21.0 (IBM Corp., Armonk, NY) and Mplus version 7.0 (Muthén & Muthén, Los Angeles, CA). Data cleaning and analyses will be performed using SPSS and Mplus syntax operations. We will conduct descriptive analyses to describe the study population. Possible baseline differences between trial arms will be statistically tested. We will adjust further analyses for imbalances in the baseline scores.

The primary analysis will be by intention to treat. As sensitivity analyses, only completers of all assessments will be analysed. The impact of the DA on the primary outcome will be analysed using *χ*^2^-tests. The numeric secondary outcomes will be analysed using analyses of variance; categorical secondary outcomes will be analysed using *χ*^2^-tests. Additionally, latent change model analyses will be performed for continuous longitudinal outcome data. Latent transition analyses will be performed for categorical longitudinal outcome data. To handle missing data, full information maximum likelihood estimation will be conducted in MPlus. To investigate the mediation and moderation effects of the secondary and demographic variables, mediation and moderation analyses will be performed using the PROCESS macro version 2.13 (Andrew F. Hayes, http://www.processmacro.org). in SPSS. As part of the questionnaire adaptation, factor, reliability, and correlation analyses will be performed.

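### The sample size assumes a one-tailed 5% test, but the primary chi-square test has no stated sidedness or alpha; run at its ordinary 5% level, power for 7 points is about 70%, not 80%

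*Protocol article*

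**What the plan says.** The Sample size section takes "a difference in the proportion of informed choices of 7 percentage points" as the minimum clinically important difference. The planned size is "A sample size of 740 women (370 per arm based on a 1:1 allocation ratio"), and this is said to detect that difference "given 80 % power and a 5 % (one-tailed) significance level". The level is marked as one-tailed directly before the recruitment assumptions ("one-tailed) significance level. Allowing for an estimated response rate of" 15%). The number of invitations follows from "an estimated response rate of 15"% and "early drop-out of one-third of initial participants".

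The Data analysis section says: "The impact of the DA on the primary outcome will be analysed using" chi-square tests. It gives no significance level, no direction and no rule for turning the chi-square p-value into a one-tailed one. It names the same kind of test, without qualification, for categorical secondary outcomes. The only mention of a tail in the document is in the Sample size section, and no section describes any test as two-sided or two-tailed.

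The primary objective, at the end of the Background, is directional: it asks whether the decision aid leads to more informed choices. No control-arm rate of informed choice is given for the calculation.

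**The concern.** The number of women was chosen for one decision rule, and the analysis as written follows a different one unless something is added. With one degree of freedom the chi-square statistic is the square of the z statistic for the difference in proportions, so it rejects for a rise or a fall in informed choice. Compared with 5% in the usual way, it requires |z| above 1.960, whereas the sample size assumed that z above 1.645 would be enough.

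One of two things follows. If the test is run in the ordinary way, the chance of missing the protocol's own minimum important difference is about 30%, not 20%. If the planned one-tailed level is applied, the decision aid is declared effective at what would be a two-sided level of 10%, with a 5% false-positive risk in its favour where 2.5% is conventional. This matters because the Abstract says that an effective decision aid will be made public and recommended.

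**Working it through.** **Inputs from the Sample size section.** 370 per arm, difference d = 0.07, one-tailed alpha 5%, power 80%. Normal quantiles: z(0.95) = 1.645, z(0.975) = 1.960, z(0.80) = 0.842.

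**1. The plan's own figures.** The invitation count reproduces: 7400 × 0.15 × 2/3 = 740. The 370 per arm cannot be reproduced from the document alone, because the control rate is missing. The pooled two-proportion formula, with p2 = p1 + 0.07 and p̄ the mean of the two, is

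n per arm = [z(1−α)·√(2p̄(1−p̄)) + z(0.80)·√(p1(1−p1) + p2(1−p2))]² / d².

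Solved backwards for n = 370 at one-tailed 5%, it needs a control rate of about 14.4% or 78.6%. These rates are back-solved, not document inputs.

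**2. Power at two-sided 5%, without a control rate.** If the design has 80% power at one-tailed 5%, the expected z is about 1.645 + 0.842 = 2.487. Power against a critical value of 1.960 is

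Φ(2.487 − 1.960) = Φ(0.527) = 70.1%.

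(Rejection in the wrong direction adds a negligible amount.)

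**3. Check at the back-solved rates.** With 370 per arm and d = 0.07, two-sided 5% power is 70.0% at both 14.4% and 78.6%. Fisher's exact test at a 13% control rate gives 79.8% one-tailed and 69.9% two-sided.

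**4. Size and difference for 80% power, two-sided.** The sample ratio is ((1.960 + 0.842)/(1.645 + 0.842))² = (2.802/2.487)² = 1.27, so 370 × 1.27 ≈ 470 per arm, or 940 in total. With 370 per arm kept, the detectable difference is roughly 7 × 2.802/2.487 = 7.9 points. The full formula gives 8.0 points at 14.4% and 7.8 at 78.6%.

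**5. How far this depends on the control rate.** The 70% inherits the stated 80%. Power for 7 points with 370 per arm under other assumed control rates:

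| Assumed control rate | One-tailed 5% | Two-sided 5% |
|---|---|---|
| 10% | 87.4% | 79.7% |
| 14% | 80.6% | 70.8% |
| 15% | 79.1% | 68.9% |
| 48% | 60.3% | 47.8% |
| 79% | 80.6% | 70.8% |
| 88% | 96.3% | 92.9% |

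The 48% and 88% are the two rates of informed choice cited in the Background. Neither is tied to the sample size calculation, which refers to a different study. Two-sided power is lower than one-tailed power in every row; how much lower depends on the rate.

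**The case against.** A reader might infer that the protocol specifies a two-sided primary test and so contradicts its own sample size. The text does not support that. The Data analysis section gives no sidedness, and in a two-by-two table a one-tailed result is obtained by halving the chi-square p-value when the difference is in the favourable direction. The only sidedness stated for the primary outcome is one-tailed, and the primary objective is directional. Taken together, these allow a coherent one-tailed design with the stated power. It can be added that how a p-value is judged is often left to an analysis plan, and that the Discussion expects no negative impact on participants.

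Nor does the secondary objective on whether the decision aid "3) changes intentions to participate in the MSP" settle the matter. It is worded without direction, but it concerns intention, not informed choice.

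A reader might also take 70% as the trial's actual power. That too goes beyond the document, because the 80% from which it is derived cannot be checked.

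What stands is that a mismatch remains under the plain reading. A chi-square test named without qualification is non-directional, and the one-tailed reading needs a step that the protocol does not state. This is more than a detail left to another document: the one-tailed level and the 80% power are both printed, and the named test in its ordinary form does not deliver them. The remark about no negative impact rests on the decision aid containing the information of usual care. It is not a reason to disregard a fall in informed choice, especially since the Information part section says that the decision aid goes beyond the standard information on outcome probabilities.

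**Conclusion.** The point holds as a mismatch between the level used for sizing and the test named for the primary analysis. It is not a written contradiction between a one-sided and a two-sided test. Run as an ordinary 5% chi-square test, the primary analysis has about 70% power for 7 points, and 80% power only for about 8 points. These figures assume that the stated 80% one-tailed power is right. The step from 80% to 70% needs no control rate, but the 80% itself does. If the test is read one-tailed, the power stands as stated, but the success criterion becomes a chi-square p-value below 10% in the favourable direction, which is neither stated nor justified. Because this governs both a stated power and what counts as success on the primary outcome, it should be settled before the data are analysed.

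**What to change.** Make the Sample size and Data analysis sections agree before analysis.

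- **Preferred:** state in the Data analysis section that the primary chi-square test is two-sided at 5%. In the Sample size section, keep the record that 740 was derived at one-tailed 5%, name the assumed control rate, and add that at two-sided 5% the power for 7 points is about 70%, or that the difference detectable with 80% power is about 8 points. Recompute both figures at the named control rate.
- **Alternative:** if the one-tailed 5% test is kept, say so in the Data analysis section, state how the chi-square p-value will be judged (against 10%, and only when the difference favours the decision aid), and justify disregarding a fall in informed choice.

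Either change is one of wording and needs no extra participants. The cost of the preferred one is a less favourable stated power. Restoring 80% at two-sided 5% would instead take about 940 women, or 940/(0.15 × 2/3) = 9,400 invitations; the fix does not require this.
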